#### Interviews With Midwives

We will conduct interviews with midwives to deepen our understanding of midwives’ perceived role and the resources that they need or already use to provide nutrition communication. In addition to the salutogenic model and appreciative inquiry, we will use the 5 A’s construct (or 5 A’s model) in these interviews. The 5 A’s—assess, advise, agree, assist, and arrange—will help to obtain insight into the extensiveness of current nutrition communication in midwifery practice, similar to Van Dillen and colleagues’ method for general practitioners [47,48].

The interviews will be conducted by 2 trained researchers. One of the researchers will primarily conduct the interview, and the other will check whether all questions have been posed and pose additional questions at the end of the interview if needed. We will alternate these roles.

#### Focus Groups

We will organize 2 rounds of semistructured focus groups to complement the individual interviews, as group dynamics may allow for new ideas to arise. The focus groups will be activity oriented where possible, by incorporating choosing, listing, and ranking activities. Such activities can, for instance, be used to test participants’ knowledge and stimulate more in-depth discussions and to make focus groups more enjoyable by doing things rather than just talking [49].

In round 1, we will conduct 2 focus groups of 4 to 12 participants for each study population (pregnant women, midwives, and dietitians) independently. In these focus groups, we will integrate data from the prior individual interviews with pregnant women and midwives and discuss the results (current practice, needs, tool suggestions, and so on) and any inconsistencies. Participants will be a combination of previous interviewees and new participants, to combine those who have already thought of the subject and those with new ideas.

After analyzing the data from the first round of focus groups, in round 2 we will organize 1 or 2 focus groups, attended by pregnant women, midwives, and dietitians combined. In this second round, we will integrate data from the previous focus groups for all participants to work toward a tool(box) together. The mixed focus groups are aimed at facilitating a cocreation process in which important stakeholders together develop the tool(box) based on the research findings.

#### Implementation and Process Evaluation

From the synthesis of the data obtained from the literature and from interviews and focus groups with pregnant women, midwives, dietitians, and experts in the field, we will develop a tool(box) or adjust an existing tool, or both. As the developed tool(box) will be cocreated with all stakeholders and based on the research findings, we cannot yet give an exact description of the tool(box). In addition, it is not yet clear in what setting or settings the tool will be implemented. The developed tool could become part of midwifery practices, be specifically directed at pregnant women, or be implemented by other health care professionals, or a combination thereof. Depending on the cocreation process, we will involve new stakeholders when needed to further develop and implement the tool(box). Experts will be mainly from the Netherlands, but we will also consult experts from countries with similar prenatal care systems.

We will pilot test the tool(box) in real-life practice, specifically for low-SES pregnant women. For the pilot, we will select 5 midwifery practices in different regions of the Netherlands, both urban and rural. We expect that the process evaluation will include approximately 100 individual consultations and 20 CenteringPregnancy group meetings. CenteringPregnancy [50] brings up to 12 pregnant women together for their care and facilitates discussion and activities to address important health topics while leaving room for what is important to the group.

To provide insight into both successes and failures in the implementation of the tool(box), we will conduct a comprehensive process evaluation. In this phase, we may use multiple research methods to understand what works and why. Depending on the eventual tool or tools developed, the methods might include questionnaires, observations through video recording, in-depth interviews, and focus groups. The evaluation will cover common components of process evaluations in public health, such as the proportion of the intended target population participating (ie, reach), how often each part of the tool(box) was delivered by midwives and actually used by pregnant women (ie, dose delivered and received), and the extent to which the intervention was delivered as planned (ie, fidelity). Additionally, it will include environmental and socioenvironmental aspects that may influence implementation (ie, context) and a description of procedures used to approach and attract participants (ie, recruitment) [51]. Lastly, the compatibility of the tool(box) with midwives’ and pregnant women’s needs and expectations (ie, satisfaction) will show whether the involvement of stakeholders in the development of the tool(box) has paid off [52].

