All research activities and project meetings conducted in the first phase of the research will contribute to the development of this tool(box) and its implementation and evaluation in the second phase. A limitation of this study is its inability to measure the effectiveness of the developed tool(box) within the scope of the study. An evaluation of the effects on dietary intake, as well as maternal and child health outcomes, could be part of a follow-up study. If the adapted or newly developed tool(box) improves pregnant women’s dietary intake, the impact on perinatal and postnatal outcomes may have health and social benefits, as well as economic benefits.

We will disseminate results to participants who express an interest in this, as inventoried at the end of the interviews. Project partners will be informed on progress, and results will be conveyed orally at least every 6 months by way of a group meeting or individual phone calls. All project partners have furthermore agreed to share the results of the research with their members, for example, through their websites or newsletters. To inform the scientific community, we will disseminate results in scientific journals, as well as at national and international conferences.

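### Satisfaction in a single-group pilot can describe how well the tool(box) fits its users, but cannot show whether stakeholder involvement paid off

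*Protocol article*

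**What the plan says.** Under Implementation and Process Evaluation, the Protocol article lists the components of the process evaluation. The last is satisfaction, meaning how compatible the tool(box) is with what midwives and pregnant women need and expect. The article says this "will show whether the involvement of stakeholders in the development of the tool(box) has paid off".

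The same section describes the pilot: "we will select 5 midwifery practices in different regions of the Netherlands, both urban and rural". It expects "approximately 100 individual consultations and 20 CenteringPregnancy group meetings" to be included. The methods are left open until the tool(box) is known.

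On who makes the tool(box), that section begins a sentence with "As the developed tool(box) will be cocreated with all stakeholders and based on the research findings". The Focus Groups section describes a second round that brings pregnant women, midwives and dietitians together, with the aim of "facilitating a cocreation process in which important stakeholders together develop the tool(box) based on the research findings".

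Under Strengths and Limitations the article concedes: "A limitation of this study is its inability to measure the effectiveness of the developed tool(box) within the scope of the study".

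**The concern.** To say that involvement has paid off is to compare the result with what would have happened without it. Nothing in the described pilot supplies that comparison. If the sentence is followed as written, a favourable satisfaction result will be reported as evidence that co-creation worked, and an unfavourable one as evidence that it did not. Neither conclusion would be supported.

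This deserves attention because the Study Design section treats stakeholder involvement as central to the project. The sentence therefore promises a judgement on the study's main working method.

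A second, weaker issue is who gives the ratings. A midwife who helped to shape the tool(box) is not an independent judge of whether it meets her needs, and the article neither says that such midwives will be among the pilot respondents nor excludes it.

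**Working it through.** No arithmetic applies. The article gives no satisfaction scale, target or sample size calculation for this component, so there is no figure to reproduce. The check is to set the relevant statements side by side.

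1. **What is claimed.** Satisfaction will settle whether involvement paid off (Implementation and Process Evaluation). This is a statement about the effect of the development process, made from a rating of the product.

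2. **What is observed.** There are 5 practices and one tool(box). No practice is described as using usual care, an unadjusted existing tool or a tool made without stakeholders. No measurement before introduction is described.

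3. **What each result could mean.**
   - High satisfaction is compatible with useful involvement. It is equally compatible with good content that would have been chosen anyway, extra attention during a pilot, or practices that were willing from the start.
   - Low satisfaction does not show that involvement failed, since a tool made without it might have been rated lower still.
   - The attribution therefore fails in both directions. What remains is a description of fit.

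4. **Whether the stated limitation covers this.** It concerns the effectiveness of the tool(box). Attributing satisfaction to how the tool(box) was made is a different inference, and the caveat does not reach it.

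5. **Whether raters are independent of developers.**
   - The features named for pilot practices are region and urban or rural location. Prior participation is not mentioned.
   - Phase 1 midwives come first from the project partners' network and then by postal code (Recruitment).
   - First-round focus groups deliberately mix earlier interviewees with new participants, and the second round develops the tool(box) (Focus Groups).
   - Midwives' needs and expectations regarding tools are themselves collected in phase 1 (Table 1). If the same midwives later rate the match with those needs, the check is partly circular.
   - The only linkage of participants' data that is described is between the diet history questionnaire and the in-depth interviews (Data Management and Analysis). None is described between phase 1 participation and pilot ratings.
   - Overlap is therefore possible, and neither stated nor excluded. For pregnant women it is likely to be small, because phase 1 comes before the pilot and most women seen in the pilot should be new. This last step is my inference from the order of the phases.

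**The case against.** The best defence is that the sentence can be read without any causal meaning. The Study Design section says that stakeholders are involved so that the tool(box) will fit women's needs and be workable for midwives. On that reading, paying off means only that the aim was reached, and satisfaction checks exactly that. The word whether leaves the direction open, the fourth research question is about barriers and facilitating factors, and the benefit of co-creation is not an outcome in Table 1. A process evaluation also does not need a control group. Much of this stands, and it is why the point is minor. It does not rescue the wording: even if fit is reached, the pilot cannot say that involvement is the reason.

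Three stronger readings are tempting, and the documents do not support them.

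- A reader might infer that satisfaction will be inflated by co-creators rating their own product. The overlap is undocumented, the setting for implementation is still open, and new stakeholders may join.
- A reader might try to put a number on that inflation. This would need a share of overlapping practices, a difference in ratings and a pooled score weighted by practice. The article gives none of these and plans no such score, and the ratings also come from pregnant women.
- A reader might conclude that practices whose midwives were interviewed should be barred from the pilot. Being interviewed about current practice does not make a midwife a developer, and the Anticipated Problems section reports that midwives are short of time and receive many research requests. Exclusion would narrow a limited pool for an uncertain gain.

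**Conclusion.** The concern holds as a matter of inference. The satisfaction component can describe perceived fit in 5 practices; it cannot show what stakeholder involvement contributed. This rests on the pilot being a single group with no comparison, which is how the article describes it, and it does not depend on any overlap between developers and raters.

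The possible overlap is an additional caution of unknown size, mainly about midwives. It supports recording and reporting prior participation, and no more than that.

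The weight is minor. Satisfaction is one descriptive component under the fourth research question, and no sample size, test or other stated figure is affected. The lack of a control arm is not itself a fault; the fault lies in the conclusion that the sentence announces.

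**What to change.** 1. **Reword the sentence** so that satisfaction will describe how well the tool(box) matches what midwives and pregnant women need and expect. Any remark on the value of stakeholder involvement should be dropped, or limited to participants' own views of it.

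2. **Record prior participation.** For each pilot respondent, note whether she took part in the co-creation focus groups or, separately, in the phase 1 interviews. This is easy to collect at the time and harder to reconstruct later.

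3. **Report satisfaction separately** for prior participants and new users. With 5 practices, keep this descriptive, and give the number of respondents in each group.

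The cost is one edited sentence and one extra recorded variable. The drawback is that some subgroups will be small, particularly among midwives, so the split will show where ratings come from without supporting a formal comparison. The choice of pilot practices need not change.

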### Data Management and Analysis

We will manage data according to Wageningen University’s research data policy, based on the Netherlands Code of Conduct for Scientific Practice and the FAIR (findability, accessibility, interoperability, and reusability) principles. All participants will be assigned a unique study identifier to store data anonymously. We will use the study identifiers to link the quantitative and qualitative data of those participating in both the DDHQ and the in-depth interviews, allowing for investigation of associations between the quality of dietary intake and individual, interpersonal, and sociocultural factors.

 We will audiotape the qualitative research data from the interviews and focus groups with the interviewees’ permission through informed consent, transcribe the audio intelligent verbatim style, and analyze the data by means of thematic analysis [53]. The thematic framework used in the analyses allows for iterative use of both deductive and inductive approaches. Interviews will be coded independently by multiple researchers to reduce interobserver bias and thereby increase the internal validity of the method. We will use ATLAS.ti version 8 software (ATLAS.ti Scientific Software Development GmbH) for these analyses to manage data and optimize transparency.

Quantitative data derived from the DDHQ will be administered and stored in the online Dutch FFQ tool [44], then exported for analysis using SAS version 9.4 statistical software (SAS Institute Inc). Food items in the DDHQ are aggregations of food codes in the Dutch Food Composition Database [54]. Total energy and nutrient intakes will be calculated automatically in the tool by multiplying frequency of intakes by consumed amounts and nutrient composition per item using the same food composition database and standard Dutch food portion sizes. We will present all DDHQ data adjusted for energy to partially account for measurement errors.

## Results

The main outcome of this study will be a tool(box) to optimize dietary intake of Dutch pregnant women. We anticipate that the developed or adjusted tool or tools will be available in February 2020. After we implement the tool(s) and evaluate the implementation process, the final results should be available by February 2021.

## Discussion

### Strengths and Limitations

This study relates to several concurrent health challenges and developments in the Netherlands, such as health inequalities, midwives’ ambition to be strengthened in their role as public health professionals, and translating the first Dutch national dietary guidelines for pregnant women (by an ad hoc committee of the Health Council of the Netherlands) into practice.

This is, to our knowledge, the first time that the dietary intake of specifically low-SES pregnant women in the Netherlands will be studied. Gaining insight into determinants of dietary intake in pregnant women, and specifically low-SES pregnant women, will help to elucidate the factors that contribute to unhealthy habits or—from a more assets-based perspective—the factors that facilitate a healthy dietary intake. By including those pregnant women who would benefit most from nutritional education, this study will address socioeconomic inequalities in health, which are considered unfair and avoidable by, among others, the WHO and governments, in an early stage of life.

The diet history method, applied in an interview by trained dietitians, is the best method for a low-SES target group. However, it is a burdensome method and not well standardized. Therefore, we developed a meal-based questionnaire with food items covering at least 95% of the intake of women of reproductive age. As we will ask additional open questions about the intake of other foods not included in the questionnaire, we expect to cover the complete dietary intake of the women like that captured by the diet history method.

All stakeholders’ perspectives need to be taken into account to generate an evidence base of what works and why in a real-life setting. The participation of multiple stakeholders (pregnant women, midwives, and other health professionals and experts) will be stimulated throughout the research, thereby generating context-sensitive and usable knowledge [55]. We will develop the tool(s) in close collaboration with pregnant women and midwives, KNOV, NVD, and NNC, taking into account their concurrent practices.

All research activities and project meetings conducted in the first phase of the research will contribute to the development of this tool(box) and its implementation and evaluation in the second phase. A limitation of this study is its inability to measure the effectiveness of the developed tool(box) within the scope of the study. An evaluation of the effects on dietary intake, as well as maternal and child health outcomes, could be part of a follow-up study. If the adapted or newly developed tool(box) improves pregnant women’s dietary intake, the impact on perinatal and postnatal outcomes may have health and social benefits, as well as economic benefits.

We will disseminate results to participants who express an interest in this, as inventoried at the end of the interviews. Project partners will be informed on progress, and results will be conveyed orally at least every 6 months by way of a group meeting or individual phone calls. All project partners have furthermore agreed to share the results of the research with their members, for example, through their websites or newsletters. To inform the scientific community, we will disseminate results in scientific journals, as well as at national and international conferences.

### Anticipated Problems

The researchers involved in this study have ample experience with the successful recruitment of low-SES pregnant groups, such as the MetSLIM lifestyle intervention [56], SLIMMER diabetes prevention intervention [57], and Communities on the Move [58]. From these experiences, we have learned that considerable efforts are required to recruit low-SES groups, that too-strict inclusion and exclusion criteria hinder recruitment, and that a personal approach and trust in the recruiter are success factors. Therefore, in this study, we allow for sufficient time for recruitment activities and have budgeted for incentives. We will ask midwives to be gatekeepers in the recruitment of pregnant women, as they have strong trust relationships with their clients. A flexible recruitment protocol will be based on the needs and desires of low-SES pregnant women and their midwives, and incentives, as stated, are budgeted for.

Compared with other countries, in the Netherlands midwives play a central role in maternity care. In general, they are interested in research that will strengthen their profession. Unfortunately, they often experience a lack of time and receive numerous requests to participate in research. We have addressed this problem by holding interviews at their location, by trying to minimize midwives’ time investment in recruitment, and by compensating them financially (based on regular hourly wages).

### Ethical Considerations

Low-SES pregnant women may be considered a vulnerable population for several reasons. First, pregnancy is a time during which women (and their unborn babies) are physically vulnerable. Second, people with a low SES may have problems understanding information. We will instruct interviewers to ensure that participants understand information correctly if the interviewers doubt comprehension and to inform the main researcher about reconsideration of participation. Researchers involved in this project are experienced with research including low-SES groups. The research as a whole is specifically responsive to the health needs and priorities of low-SES pregnant women and ultimately aims to reduce health inequalities.

We are aware of pregnant women’s dependence on midwives and shall therefore emphasize to midwives that all participants should enter the study freely. Participants will not run any physical, social, or political risk by participating in this research.

All participants will be informed about the aims of the research, duration of interviews, data preparation and anonymous data storage, the voluntary nature of participation, and their right to withdraw at any time prior to each research activity. After an opportunity to ask questions, written informed consent will be obtained from each study participant for each research activity. The term low SES, which sounds negative, will not be used in any communication with pregnant women.

### Conclusion

To our knowledge, this will be the first study to address the dietary intake of low–socioeconomic status pregnant women in the Netherlands and to link dietary intake to contextual factors by using an ecological perspective on health. We hope the results obtained will inform multidisciplinary strategies to promote a healthy dietary intake in prenatal care, specifically in low–socioeconomic status populations in developed countries.

## Appendix

Multimedia Appendix 1 Peer-reviewer report #1 from the Edema-Steernberg Foundation.

Multimedia Appendix 2 Peer-reviewer report #2 from the Edema-Steernberg Foundation.

Multimedia Appendix 3 Peer-reviewer report #3 from the Edema-Steernberg Foundation.

